#### Safety End Point

The safety end point is to assess the rate of adverse events (AEs), adverse device effects, and abnormality of laboratory parameters between the 2 treatment groups across the study (ie, V1, V2, and V3).

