### Treatment Arms

In the intervention group (group A), the NP and PA program are administered through KidneYou, supplemented by guided stress-reduction activities.

In the control group (group B), the NP and PA program are administered by means of a paper diary. No indications are given to patients in this group regarding stress reduction activities.

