### Assessments

Each participant undergoes 4 visits and is examined according to the following schedule: baseline (V0), 6-week visit (V1), 12-week visit (V2), and 4-week follow-up visit (V3). During the baseline visit, the patient signs the informed consent form and is evaluated for inclusion and exclusion criteria. Once enrollment is confirmed, the patient is randomized. The PSS questionnaire is administered to all enrolled patients, regardless of the randomization group. At V0, V1, V2, and V3, a complete physical examination is performed; vital signs (systolic blood pressure, diastolic blood pressure, HR, and respiratory rate), ongoing medications for CKD, and concomitant medications are collected.

At V0, V2, and V3, laboratory tests are also performed and include hematology (complete blood count, glycemia, proteins [albumin], and creatinine), minerals (phosphorus and calcium), electrolytes (sodium, potassium, chloride, and bicarbonate), azotemia, and uric acid; lipid profile, that is, total cholesterol, high-density lipoprotein cholesterol, low-density lipoprotein cholesterol, and triglycerides; and urine tests (24 h urinary excretion collection), that is, urea nitrogen, uric acid, minerals (phosphorus and calcium), electrolytes (potassium, sodium, chloride, and bicarbonate), albumin, creatinine, glucose, density, pH, proteins, ketones, hemoglobin, bilirubin, nitrites, white cells, red blood cells, casts, crystals, epithelial cells, and serum pregnancy test, only for women of childbearing potential.

All patients undergo the 6-MWT and bioimpedance test. Safety, including the appearance of adverse device effects and abnormalities in physical and laboratory parameters, is assessed throughout the entire study period.

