#### Safety

Medical AEs, medical device AEs, and laboratory parameter abnormalities will be collected during the study.

Medical AEs will be coded to a preferred term and primary system organ class, using the current version of the *Medical Dictionary for Regulatory Activities* (MedDRA; International Council for Harmonisation of Technical Requirements for Pharmaceuticals for Human Use) dictionary. AEs will be tabulated as preferred term, system organ class, and frequency for the safety population.

The statistical difference in the rate of AEs, device AEs, and laboratory parameter abnormalities will be assessed through the chi-square test or the Fisher exact test.

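### Device adverse events are tested against a control arm that has no device, and the laboratory abnormality rate conflicts with the laboratory schedule and is not tied to baseline

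*Protocol article*

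**What the plan says.** All references are to the protocol article.

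- **Safety End Point.** One visit list serves adverse events, adverse device effects and laboratory values. The last of these reads "abnormality of laboratory parameters between the 2 treatment groups across the study (ie, V1, V2, and V3".
- **Assessments, laboratory.** "At V0, V2, and V3, laboratory tests are also performed". V1 does not appear in that list.
- **Assessments, V1.** "At V0, V1, V2, and V3, a complete physical examination is performed", together with vital signs and medications.
- **Assessments, safety.** "Safety, including the appearance of adverse device effects and abnormalities in physical and laboratory parameters, is assessed throughout the entire study period".
- **Statistics, Safety.** "The statistical difference in the rate of AEs, device AEs, and laboratory parameter abnormalities will be assessed through the chi-square test", with Fisher's exact method as the alternative.
- **Treatment Arms.** In the control group, "the NP and PA program are administered by means of a paper diary". No app is given.
- **Inclusion criteria.** GFR must be in category G3b or G4 (15-44 mL/min/1.73 m²). Albuminuria may be A1, A2 or A3, so normal albuminuria is admitted.
- **Tertiary or Exploratory End Points.** Changes in blood and urine levels are compared over V0, V2 and V3.

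**The concern.** Three parts of the stated safety analysis do not fit the design.

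1. A device adverse event needs a device. Testing its rate against an arm without one compares a count with a fixed zero. A result above 0.05 could be read as reassurance and one below it as a signal, when either only reports how many app users had an event.
2. A laboratory end point is placed at V1, where no laboratory test is scheduled.
3. The tested laboratory quantity is a rate of abnormality with no stated link to V0. Everyone enters with reduced GFR, so a GFR-linked value such as creatinine may be abnormal in nearly all patients before treatment. A plain count of abnormal values would then barely register deterioration.

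Safety is part of the stated objective, and the study is premarket evidence for CE marking. The safety tables should therefore answer a question that the design can answer.

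**Working it through.** **Arm size.** No figure is stated for the safety comparison, so the arm sizes come from the Sample Size Calculation: 95 evaluable and 105 enrolled per group. The 95 reproduces with unpooled variance: (1.960 + 0.842)² × (0.4×0.6 + 0.6×0.4) / 0.20² = 94.2, rounded up to 95. It serves below only as an arm size.

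**Device events.** With n per arm, k events in the app arm and 0 in control, the two-sided Fisher p-value is

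p = 2 × C(n, k) / C(2n, k).

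For n = 105, k = 6: 2 × (105·104·103·102·101·100) / (210·209·208·207·206·205) = 0.029. The exact (Clopper-Pearson) 95% CI for the app arm takes the 0.025 quantile of Beta(k, n−k+1) and the 0.975 quantile of Beta(k+1, n−k).

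| n per arm | events, app v control | Fisher p | app-arm rate | exact 95% CI |
|---|---|---|---|---|
| 105 | 5 v 0 | 0.060 | 4.8% | 1.6% to 10.8% |
| 105 | 6 v 0 | 0.029 | 5.7% | 2.1% to 12.0% |
| 95 | 5 v 0 | 0.059 | 5.3% | 1.7% to 11.9% |
| 95 | 6 v 0 | 0.029 | 6.3% | 2.4% to 13.2% |

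The formula contains nothing but n and k. One more event takes the result across 0.05, while the app-arm rate and its interval hardly move.

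**Visit lists side by side.**

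| | V0 | V1 | V2 | V3 |
|---|---|---|---|---|
| Safety End Point (laboratory abnormality) | no | yes | yes | yes |
| Assessments (laboratory tests) | yes | no | yes | yes |
| Exploratory laboratory changes | yes | no | yes | yes |

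The first row disagrees with the other two at V1, and V2 and V3 are the only visits common to all three.

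**Dilution if V0 is ignored.** Let b be the share already abnormal at V0, and assume that these patients stay abnormal. Among the rest, assume new abnormality in 10% of one arm and 25% of the other. The document gives neither b nor these rates, so b is run over a range. The crude rates are

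p1 = b + (1−b)×0.10 and p2 = b + (1−b)×0.25, so p2 − p1 = 0.15×(1−b).

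Power = Φ[(p2 − p1 − 1.96×s0) / s1], with s0 the pooled and s1 the unpooled standard error and n = 95. For b = 0: s0 = 0.0551 and s1 = 0.0540, so (0.15 − 0.1081)/0.0540 = 0.776 and power is 78%.

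| b | crude rates | power |
|---|---|---|
| 0% | 10.0% v 25.0% | 78% |
| 25% | 32.5% v 43.8% | 36% |
| 50% | 55.0% v 62.5% | 18% |
| 75% | 77.5% v 81.3% | 9% |
| 90% | 91.0% v 92.5% | 6% |
| 100% | 100% v 100% | no contrast |

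**The case against.** **The V1 entry is a loose shared list.** It covers three items and is right for adverse events and device effects. No V1 laboratory data are scheduled, so none can be misanalysed. This stands: the mismatch alone changes no result, but the two sections still disagree.

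**The article does not say that V0 is ignored.** Naming post-baseline visits does not rule out V0 as the reference. The Assessments section speaks of abnormalities appearing, which can be read as new ones, and a definition may sit in the full plan. This stands too. The dilution is what would follow if the rate were counted without V0, not a demonstrated error.

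**Laboratory change is compared elsewhere.** The exploratory end points compare changes over V0, V2 and V3, blood creatinine included. That covers part of the gap, but a difference in mean change is not a count of patients who worsened.

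**No decision rule hangs on these p-values.** The safety objective is descriptive. That lowers the stakes. It does not give the device-event test a comparator, and the objective itself points to description.

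**A stronger reading.** A reader might infer that the whole safety comparison cannot inform, because patients are abnormal by eligibility. The document does not support that. The comparison of all adverse events is sound. Eligibility fixes reduced GFR only: A1 albuminuria is admitted, and no entry limit is listed for sodium, potassium or lipids, for example. Randomisation keeps the V2 and V3 laboratory comparisons valid, and the loss of contrast varies by parameter.

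**Conclusion.** The point holds in three limited parts.

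- **Device events (firmest).** The control rate is zero by construction, assuming no control participant obtains the app. The between-arm p-value is then a function of the app-arm count alone, crossing 0.05 between 5 and 6 events at either arm size, and it carries no safety information.
- **V1.** The Safety End Point and Assessments sections contradict each other on laboratory data at V1 and must be reconciled. The effect on results is nil.
- **Laboratory abnormality.** The tested rate is not tied to V0. If V0 is ignored, contrast shrinks in proportion to (1−b), with little or none left for GFR-linked values such as creatinine. The fall in power from 78% to 6% rests on the assumed 10% v 25% rates and on b between 0% and 90%. It does not describe the whole laboratory panel.

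This should be put right because the changes are nearly free and improve what the safety analysis can conclude. It does not threaten the trial's validity.

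**What to change.** 1. Drop the between-arm test of device adverse events. Report adverse device effects in the app arm only, as number and percentage with an exact 95% CI. Keep the between-arm comparison for all adverse events.
2. Reconcile the V1 reference in the Safety End Point with the laboratory schedule in Assessments, giving laboratory values their own visit list.
3. Define laboratory abnormality as a value at V2 or V3 that is new or worsened relative to V0, state how worsening is judged for each parameter, and compare that between arms.

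The cost is wording and table shells. The V0, V2 and V3 laboratory values are already scheduled, so no new data are needed. The Results section says that analysis is ongoing, so the change should be documented and dated, with a note on whether safety data by arm had been seen.

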#### Tertiary or Exploratory End Points

The tertiary or exploratory end points are as follows:

To assess the between-group differences in changes of mean values of PA (min) self-reported by patients during the study visits (ie, V0, V2, and V3)To assess the within-group changes and the between-group differences in changes of urinary levels of phosphorus, calcium, potassium, sodium, chlorine, bicarbonate, albumin, creatinine, glucose, and uric acid by urine samples during the study visits (ie, V0, V2, and V3)To assess the within-group changes and the between-group differences in changes of urinary levels of other compounds (ie, density, pH, proteins, ketones, hemoglobin, bilirubin, nitrites, white cells, red blood cells, casts, crystals, and epithelial cells) by urine samples during the study visits (ie, V0, V2, and V3)To assess the within-group changes and the between-group differences of changes in blood levels of electrolytes (potassium, sodium, chloride, and bicarbonate), minerals (phosphorus and calcium), proteins (albumin), metabolic products (nitrogen and creatinine), sugar (glucose), and uric acid in the blood samples during the study visits (ie, V0, V2, and V3)To assess the within-group changes and the between-group differences of changes of vital signs (systolic blood pressure or diastolic blood pressure, HR, and respiratory rate) during the study visits (ie, V0, V1, V2, and V3)To assess the between-group differences of changes in mean values of impedancemetry (lean mass and fat mass) during the study visits (ie, V0, V2, and V3)To assess the within-group changes and the between-group differences of changes of signs and symptoms characterizing CKD during the study visits (ie, V0, V1, V2, and V3)To assess the within-group compliance (adherence) by measuring the overall time (min) of KidneYou use during the 3 months of the studyTo assess a possible correlation between levels of compliance with KidneYou use and the rate of achievement of the primary end pointTo assess a possible correlation between levels of compliance (min) with KidneYou and the customer experience rate according to Net Promoter Score

### Assessments

Each participant undergoes 4 visits and is examined according to the following schedule: baseline (V0), 6-week visit (V1), 12-week visit (V2), and 4-week follow-up visit (V3). During the baseline visit, the patient signs the informed consent form and is evaluated for inclusion and exclusion criteria. Once enrollment is confirmed, the patient is randomized. The PSS questionnaire is administered to all enrolled patients, regardless of the randomization group. At V0, V1, V2, and V3, a complete physical examination is performed; vital signs (systolic blood pressure, diastolic blood pressure, HR, and respiratory rate), ongoing medications for CKD, and concomitant medications are collected.

At V0, V2, and V3, laboratory tests are also performed and include hematology (complete blood count, glycemia, proteins [albumin], and creatinine), minerals (phosphorus and calcium), electrolytes (sodium, potassium, chloride, and bicarbonate), azotemia, and uric acid; lipid profile, that is, total cholesterol, high-density lipoprotein cholesterol, low-density lipoprotein cholesterol, and triglycerides; and urine tests (24 h urinary excretion collection), that is, urea nitrogen, uric acid, minerals (phosphorus and calcium), electrolytes (potassium, sodium, chloride, and bicarbonate), albumin, creatinine, glucose, density, pH, proteins, ketones, hemoglobin, bilirubin, nitrites, white cells, red blood cells, casts, crystals, epithelial cells, and serum pregnancy test, only for women of childbearing potential.

All patients undergo the 6-MWT and bioimpedance test. Safety, including the appearance of adverse device effects and abnormalities in physical and laboratory parameters, is assessed throughout the entire study period.

### Data Collection and Management

The KidneYou software consists of 3 different components.

The mobile app enables the patient to receive dietary indications, exercise categories, and mindfulness content and to enter information related to the activities performed. It also allows the patient to provide feedback through questions and evaluations on the activities performed.

The ICE Platform, which can be accessed through a dedicated control panel after authentication and authorization, allows the physician to enter patient data into the platform. The platform also displays data on patient adherence to recommended activities.

The backend is the part of the software dedicated to exchanging communications between the mobile app and the ICE platform. It receives patient input from the app, including self-reported adherence to activities, which is sent to the platform for visualization.

The KidneYou database has been developed using EDC technology (ICE, Advice Pharma), compliant with the regulations for clinical data management to facilitate the study data analysis.

Data are collected for each participant in eCRFs. The eCRF is designed by Advice Pharma Group using the ICE software.

ICE (version 2.6.2) is the EDC solution provided by Advice Pharma. This system is a fully web-based Integrated Development Environment designed to generate customizable eCRFs.

The EDC system consists of the database application and integrated tools for query management and audit trail. Data are reviewed and checked for completeness and validity before, during, and after data entry. The data cleaning process includes different levels of control: source data verification and quality checks at the data entry level, automatic controls on the ICE database, and database data review performed by the data manager, with the production of manual eQueries.

Entered data are subject to visual and electronic validation by data management and monitoring staff. Any errors, inconsistencies, and unexpected values in the data are noted and queried with the site staff for resolution.

The data manager reviews data for each patient upon study withdrawal, after all data are entered, and after source data verification is completed. Data cleaning continues until all discrepancies are resolved. Data changes resulting from queries are made by the investigator directly in the clinical database.

Concomitant medications are coded using the latest available version of the *World Health Organization Drug Dictionary Enhanced* (WHO DDE). The data manager performs the coding centrally using the dedicated ICE coding tool, matching the term entered by the investigator with the appropriate term in the relevant dictionary.

Medical coding is performed at the end of the study before database lock.

### Statistics

#### Sample Size Calculation

This study is designed to test the null hypothesis that the percentage *success* (defined by the achievement of at least one of the 3 conditions described in the primary end point, with no hierarchical structure among them) in KidneYou nonusers is equal to the percentage “success” in KidneYou users. The alternative hypothesis is that the percentage “success” in KidneYou nonusers is different from the percentage “success” in KidneYou users.

The sample size is estimated to assess the study hypothesis on the primary end point.

The sample size calculation is based on the combination of the expected proportion of success in the control group and the expected delta (Δ) of success in the experimental group.

With a significance level α equal to .05 and a power equal to 80%, a sample size of 190 participants (95 per group) is required to detect as significant, if any, a success delta in favor of the experimental group equal to 20% (under the hypothesis of success rate of 40% in the control group and success rate of 60% in the experimental group). Considering a dropout rate of approximately 10%, a total of 210 patients (105 per group) will have to be enrolled. A competitive enrollment approach across the centers involved in the study will be used to reach the sample size efficiently.

#### Statistical Analysis

All the analyses on primary, secondary, and tertiary or exploratory end points will be carried out in the intention-to-treat population—as main analyses—and in per protocol population, as sensitivity analyses. Safety end points will be described only for the per protocol population.

Data will be analyzed and presented in accordance with the international CONSORT (Consolidated Standards of Reporting Trials) guidelines and analyzed according to the intention-to-treat principle.

Data analyses will be conducted using SAS (version 9.4; SAS Institute) statistical software.

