### Study Design

This is a multicenter, randomized, 2-arm, comparative, parallel, open-label, premarket study on individuals affected by CKD belonging to GFR categories G3b or G4, and with persistent albuminuria categories A1, A2, or A3 (A3 limited to >300 mg/g [>30 mg/mmol] and <3000 mg/g [<300 mg/mmol]).

This study is a premarket clinical investigation conducted in accordance with European Union Medical Device Regulation n.2017/745 requirements, with the goal of generating clinical evidence necessary for Conformité Européenne marking of the investigational medical device.

Enrolled participants are randomly allocated in a ratio of 1:1 to one of the two treatment arms using a randomization list that is computer generated by the trial statistician and provided through a web-based approach (via interactive response technology or randomization and trial supply management): group A (KidneYou users; investigational arm) or group B (KidneYou nonusers; control arm). A randomization list with random permuted blocks of different sizes (2 or 4 or 6 or 8) has been prepared and included in the electronic case report form (eCRF).

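### The plan gives two conflicting populations for safety; if the per protocol rule is followed, adverse event counts can only fall and rates are likely to be understated

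*Protocol article*

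**What the plan says.** Three parts of the protocol article bear on this.

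- **Safety End Point:** "The safety end point is to assess the rate of adverse events (AEs), adverse device effects, and abnormality of laboratory parameters", compared between the two groups across V1, V2 and V3.
- **Statistical Analysis:** efficacy end points are analysed "in the intention-to-treat population—as main analyses—and in per protocol population, as sensitivity analyses". The next sentence turns to safety: "Safety end points will be described only for the per protocol population".
- **Safety (under Statistics):** "AEs will be tabulated as preferred term, system organ class, and frequency for the safety population". The section then adds: "The statistical difference in the rate of AEs, device AEs, and laboratory parameter abnormalities will be assessed through the chi-square test" (Fisher's exact test is the alternative). No population is attached to these tests.

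The article defines neither the per protocol population nor the safety population, and it does not say that they are the same set.

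**The concern.** The first rule contains the word only, so it leaves no room for a second safety set. The Safety section then uses a different one. A programmer working from this text could not tell which patients belong in the AE tables, and would have to choose a set for the tests unaided.

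The choice matters because a per protocol set is selected after randomisation. In its usual sense it drops patients who stop the programme, deviate from it or withdraw, and an AE is one reason for doing so. The trial is open-label, and group A receives mindfulness content that group B does not, so the number and type of exclusions may also differ by arm. That would distort the between-group comparison that the safety end point calls for.

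Safety is part of the study's stated aim. The trial is a premarket device investigation meant to supply evidence for CE marking, so the aggregate safety tables carry weight.

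**Working it through.** **Step 1. Compare the two rules.**

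| Item | Statistical Analysis section | Safety section |
|---|---|---|
| AE tables | per protocol only | safety population |
| Device AEs and laboratory abnormalities, description | per protocol only | no population clearly named |
| Between-group tests | not mentioned | no population named |

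The sentence just before the safety rule uses per protocol in the ordinary way, as the restricted sensitivity set set against intention to treat. The same term one sentence later should carry the same meaning. On that reading efficacy is analysed mainly in the full randomised population, and safety only in the restricted one.

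**Step 2. Reproduce the plan's own figures, which supply the denominators.** The inputs come from Sample Size Calculation and Study Design: success of 40% against 60%, two-sided alpha 0.05, power 80%, allocation 1:1.

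- Unpooled normal approximation: n = (1.960 + 0.842)² × (0.4×0.6 + 0.6×0.4) / 0.20² = 7.85 × 0.48 / 0.04 = 94.2, which rounds up to 95 per group. This matches the plan. The pooled formula gives 97.
- Dropout: 95 × 1.10 = 104.5, which rounds up to 105 per group, or 210 in total. This also matches. (190 / 0.90 gives 212, a trivial difference.)

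The sample size plays no part in the conflict. It does show that, if only the planned dropouts leave, the per protocol set loses 105 − 95 = 10 patients per arm, or 20 of 210 (9.5%), with all their events. Other deviations could remove more.

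**Step 3. Illustrate the effect on AE rates.** The documents give no AE rates, so those below are assumed. With 95 retained and 10 removed per arm:

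all-patient rate = (95 × rate in retained + 10 × rate in removed) / 105

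relative shortfall = 1 − (rate in retained / all-patient rate)

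| AE rate in retained (per protocol figure) | AE rate in removed | All-patient rate | Relative shortfall |
|---|---|---|---|
| 10% | 5% | (9.5 + 0.5)/105 = 9.5% | −5% (overstated) |
| 10% | 10% | (9.5 + 1)/105 = 10.0% | 0% |
| 10% | 20% | (9.5 + 2)/105 = 11.0% | 9% |
| 10% | 30% | (9.5 + 3)/105 = 11.9% | 16% |
| 10% | 50% | (9.5 + 5)/105 = 13.8% | 28% |
| 10% | 80% | (9.5 + 8)/105 = 16.7% | 40% |
| 5% | 50% | (4.75 + 5)/105 = 9.3% | 46% |

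**Step 4. Consider a difference between arms.** Suppose both arms have 10% among retained patients, but 50% of those removed in one arm and 10% in the other had an AE. The per protocol tables show 10% against 10%. The all-patient rates are 13.8% against 10.0%. A difference of 3.8 percentage points disappears.

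**The case against.** The strongest reply is that the dedicated Safety section already assigns AE tabulation to the safety population. If that section governs, the AE tables are sound. This is fair, and it means understatement is a risk attached to one of two rules and not a settled consequence. It does not remove the conflict. It also leaves open the population for the tests and, since the tabulation sentence follows directly on the coding of medical AEs, arguably that for device effects and laboratory abnormalities.

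A reader might infer that the plan simply understates harms. The documents do not support so firm a statement, for two reasons. First, the per protocol set is undefined in the article, so who leaves it is inferred from common usage. Second, a lower AE rate requires that removed patients have more AEs than retained ones. Patients may also leave for reasons unrelated to harm, such as missed visits, and the table includes cases of no bias and slight overstatement.

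A reader might also produce larger distortions. With a true rate of 10% in 105 patients and half of those with an AE leaving, the reported rate is 5.25/99.75 = 5.3%; with 80% leaving it is 2.1/96.6 = 2.2%. That arithmetic is correct, but it assumes that nobody without an AE leaves, and the exit fractions have no source in the documents. If 10 leave per arm and they include 20% of the 10.5 patients with an AE, the reported rate is 8.4/95 = 8.8%.

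Finally, the reach is limited. The primary analysis is untouched. Safety is assessed over the whole study, and the Monitoring section has AEs and serious AEs reported as regulations require. The defect lies in the aggregate tables and tests, not in the detection of events.

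The definitions themselves may properly sit in the full protocol or the SAP, and their absence is not the point. The point is that the article states a rule and then contradicts it.

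**Conclusion.** The conflict is real and unresolved: one section confines safety to the per protocol population, another uses the safety population for AE tables, and none is named for the tests.

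If the per protocol rule is followed, and the term has its usual meaning, AE counts can fall but never rise, and AE rates are likely to be understated. With 10 of 105 patients per arm removed and an assumed 10% rate among those retained, the relative shortfall runs from none to 40% as the rate among those removed goes from 10% to 80%. It reverses slightly if removed patients had fewer AEs. These figures are illustrations, since the documents give neither AE rates nor the size of the per protocol set.

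The correction should be made before the safety analysis is finalised.

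**What to change.** In the Statistical Analysis section, delete the restriction of safety to the per protocol population. State that all safety end points (AEs, device effects and laboratory abnormalities) use the safety population, for the tables and for the chi-square or Fisher exact tests alike. If the full protocol already defines that population, refer to its definition. If not, add one, for example all randomised patients who started their assigned programme. Per protocol safety results may be kept as supplementary.

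The cost is small. It is one sentence, plus a definition if none exists, recorded as a change because the article reports that analysis is under way. Safety data are already being collected throughout the study, all 210 patients are enrolled, and no sample-size figure changes. The downside for the sponsor is that reported AE rates may be slightly less favourable.
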